#### Intervention costs

Apart from health care uptake, the costs of developing and maintaining the online bCBT platform will be taken into account, as well as the costs of weekly therapist feedback in the bCBT condition.

#### Non-medical costs

Direct non-medical costs, or *patients’ out-of-pocket expenses*, such as the cost of traveling to attend health services and the costs associated with the time spent by patients travelling, waiting and receiving treatment, are determined in accordance with the standard cost prices as listed in the relevant Dutch guidelines for economic evaluation [55].

Indirect non-medical costs, stemming from productivity losses due to absenteeism and lower efficiency levels while at work, are assessed with the second part of the Trimbos/iMTA questionnaire for Costs associated with Psychiatric Illness (TiC-P) [54], which evaluates productivity losses in the past four weeks. It will be administered at all time points (T0-T3). The questionnaire consists of 12 questions that focus on the number of days absent from work and the number of days with reduced efficiency due to feeling ill. The costs of productivity losses will be based on the gender and age specific friction costs, as outlined in the Dutch guideline for costing [55].

### Other variables of interest

#### General patient characteristics

Information on general demographic variables such as age, gender, marital status, income and educational level and data on patients’ professional and personal computer use will be collected at baseline.

#### Treatment preference

In order to determine whether this influences treatment outcomes, patients are asked what their treatment preference would have been, before they are informed about their actual treatment allocation. The possible answers are preference for bCBT or a preference for CBTAU. Whether or not the preference matches the treatment allocation will be taken into account.

#### Mastery

The 5-item version of the Mastery Scale [56] is administered at all time points (T0-T3) to assess changes in locus of control. Item scores range from 1 to 5, resulting in total scores ranging from 5 to 25, with higher scores being indicative of a higher degree of perceived control. The scale has good psychometric properties [56].

#### Work alliance

The Revised Short Version of the Work Alliance Inventory (WAI-SR) [57,58] is administered to both patients and therapists in order to determine the quality of the therapeutic alliance at T1. Item scores range from 1 to 5. The total score ranges from 12 to 60, with higher scores reflecting a better alliance between therapist and patient. The questionnaire has highly acceptable psychometric properties [58].

#### Depressive cognitions

The 14-item depression scale of the Cognition Checklist [59] will be administered at all time points (T0-T3) to assess the frequency of automatic thoughts relevant to depression. The items assess the frequency with which a thought typically occurs. Item scores range from 0 to 4. Total scores range from 0 to 56 with higher scores being indicative of more frequent negative depressive cognitions. The convergent and discriminant validity of the subscale has been found to be high [60].

#### Treatment evaluation

The 8-item Client Satisfaction Questionnaire-8 (CSQ-8) [61] will be administered at T3 to determine general satisfaction with treatment. High internal consistency has been reported [62]. In addition, the 10-item System Usability Scale (SUS) [63] will be administered to participants randomized to bCBT at T2 in order to evaluate the online blended treatment platform. The questionnaire has been found to be reliable [64].

#### Process data

Data for process analyses will be obtained from the administration offices of participating mental health care institutions and through usage statistics on the online platform. In addition, we will perform qualitative interviews with a random selection of ten patients per treatment group after Week 30. The interviews will focus on the feasibility and usability of the CBT treatment provided.

In the process analyses, we will also include the aspects that serve as input for the study flow chart in accordance with the CONSORT guidelines [36,38], such as exclusions, as well as study and treatment withdrawal rates for each group, including reasons. In addition, we will assess:The extent to which other treatments were provided in parallel with bCBT or CBTAU, such as pharmacotherapy, and the nature of this treatment.The total number of online sessions and/or face-to-face contacts and cancellations (amount of therapy received);Time investment by both the patient and the therapist. In the bCBT group, time investment can be calculated based on the number of face-to-face contacts and the amount of time spent working on the online platform. In the CBTAU group, time investment will be estimated based on the number of face-to-face contacts.Adverse effects.

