#### Cognitive behavioural treatment-as-usual (CBTAU)

In the CBTAU condition, patients receive, on average, twenty 45-minute sessions of face-to-face CBT over 20 weeks (one session per week). Therapists follow an established face-to-face CBT protocol [39] that contains the components referred to above. Therapists are required to include all four elements of CBT, but are free to decide how many sessions are spent on each module.

All individual sessions should involve monitoring of depressive symptoms, addressing the week gone by and current issues, and discussing information and homework exercises for the previous week and the week to come. Sessions will be concluded with a summary and evaluation. Patients receive their homework exercises on paper.

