#### Blended cognitive behavioural treatment (bCBT)

For the bCBT group, the existing CBT protocol [39] is divided over ten 45-minute face-to-face sessions and nine online sessions. The treatment will be delivered over a period of ten weeks (one face-to-face and one online session per week). Treatment starts and ends with a face-to-face session. The therapist follows a fixed treatment protocol. The blended face-to-face sessions are structured in a similar way to the regular face-to-face sessions, leaving the therapist room to respond to the individual patient’s needs in each session. During the sessions, the patient and therapist are logged in on the personal patient environment in the online platform.

The online platform is a secure web-based environment (Minddistrict; www.minddistrict.com). Patients and therapists access this platform with a personalized login. The website offers information that reinforces and develops on the content of the face-to-face sessions. A short video fragment is included in each online session in which a therapist explains the theory in lay terms.

In addition, patients use the website to complete homework exercises, such as monitoring their activities, feelings, thoughts and behaviour. Testimonials from two fictional patients are provided to give insight in how the exercises can be executed.

Therapists monitor their patients’ online progress and provide feedback each week before the next face-to-face session. The feedback messages take approximately 15 minutes to write and are sent on the online platform to ensure secure communication.

On completion of treatment, patients can continue to access the online treatment platform to reread information and look up homework exercises, such as the relapse prevention plan.

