#### Severity of depressive symptoms

The 28-item self-report version of the Inventory of Depressive Symptoms (IDS-SR) will be used to measure the severity of depressive symptoms [40]. The IDS-SR will be administered at all time points (T0-T3). Each item has four response categories, with scores ranging from 0 to 3. The total score ranges from 0 to 84, with higher scores being indicative of a higher severity of depressive symptoms. The IDS-SR has highly acceptable psychometric properties and has been proven to be sensitive to treatment effects in depressed outpatients [41-43]. Patients with a ≥50% symptom reduction on the IDS-SR will be deemed to be treatment responders. Remission is defined as an IDS-SR score of 13 or less, which is indicative of no depression severity [42].

A shortened version of the IDS-SR, the 16-item Quick Inventory of Depressive Symptomatology (QIDS-SR) [44] is administered within both treatment conditions to monitor the depressive symptom change trajectory more closely. Patients are encouraged to complete the QIDS-SR on a weekly basis. The questionnaire has highly acceptable psychometric properties [44].

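### Adverse effects appear only as a process item, and no patient-level worsening is compared between arms although the IDS-SR data would allow it

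*Protocol article*

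**What the plan says.** Adverse effects are named once, under Process data, as the closing item of a list: "In the CBTAU group, time investment will be estimated based on the number of face-to-face contacts.Adverse effects". The section opens with the sources: "Data for process analyses will be obtained from the administration offices of participating mental health care institutions and through usage statistics on the online platform". It then adds that "we will perform qualitative interviews with a random selection of ten patients per treatment group after Week 30", with feasibility and usability as the topic, and that the process analyses will include "study and treatment withdrawal rates for each group, including reasons".

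The arms differ in what these sources can see. The platform belongs to bCBT: the System Usability Scale "will be administered to participants randomized to bCBT at T2 in order to evaluate the online blended treatment platform", while in CBTAU "Patients receive their homework exercises on paper". The contact schedule differs too. For bCBT, "The treatment will be delivered over a period of ten weeks (one face-to-face and one online session per week"); for CBTAU the article gives about twenty face-to-face sessions over 20 weeks.

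On outcomes, Severity of depressive symptoms states that "Patients with a ≥50% symptom reduction on the IDS-SR will be deemed to be treatment responders", and sets remission at an IDS-SR score of 13 or less. The cost-effectiveness analysis uses response and DSM-IV depression status at week 30, and the cost-utility analysis uses QALYs. Explorative analyses fits a mixed model to continuous severity at T1 to T3. No section defines a deterioration outcome.

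**The concern.** The trial is meant to advise patients, providers and insurers on whether a larger trial is worthwhile, for a treatment with half the face-to-face sessions (10 against about 20). Its premise is that clinical effect is maintained. A reader will therefore want to know whether more patients get worse with less contact.

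As written, the plan does not answer that on equal terms. Adverse effects sit under sources that depend on what happens to be recorded, and the opportunity to record differs by arm. The outcomes that are measured identically in both arms are summarised either in one direction only or as averages. A patient who clearly worsens is counted with one who did not change.

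**Working it through.** The article gives no harm rate and no figure of its own to reproduce on this point. Its sample size, 2 × 75 = 150, was chosen for stability of the acceptability curve and is used here only as the number per arm.

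**1. Opportunity for passive capture.** In weeks 11 to 20, CBTAU patients still have weekly sessions while bCBT patients have finished, a gap of 20 − 10 = 10 weeks. Up to week 10, bCBT has platform contact that CBTAU lacks. The two features pull in opposite directions. Process data already measures one item differently by arm: therapist and patient time comes from contacts plus platform time in bCBT, and from contacts alone in CBTAU.

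**2. What unequal capture could do (illustration; capture rates are assumptions).** Observed rate = true rate × capture probability. Take the same true rate in both arms, with capture 0.80 in one and 0.50 in the other:

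| True rate | Observed rates | Expected patients per 75 |
|---|---|---|
| 5% | 4.0% vs 2.5% | 3.0 vs 1.9 |
| 10% | 8.0% vs 5.0% | 6.0 vs 3.8 |
| 20% | 16.0% vs 10.0% | 12.0 vs 7.5 |

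The spurious ratio is 0.80/0.50 = 1.6, or 0.50/0.80 = 0.625 if the better capture is in the other arm. With equal capture it is 1.0.

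**3. What each planned summary shows about worsening.**
- Response and remission: improvement only.
- MDD status: every patient has MDD at entry, so relative to baseline it can only persist or resolve.
- Full MINI at T3: can show new comorbid disorders; its stated purpose is current MDD and comorbidity.
- Continuous IDS-SR and QALYs: can move in either direction, but are compared as means. If a share q worsens by b points and the rest improve by a points, the mean change (1 − q)a − qb is still an improvement whenever q < a/(a + b). With a = b, that is any q below one half.

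**4. What a deterioration count would give.** For equal rates p in both arms and n = 75, before attrition, the 95% half-width for the difference is 1.96 × √(2p(1 − p)/n):
- p = 0.05: 1.96 × √(0.095/75) = 0.070
- p = 0.07: 1.96 × √(0.1302/75) = 0.082
- p = 0.10: 1.96 × √(0.18/75) = 0.096

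For 5% against 15% (two-sided 5%), the pooled standard error is √(2 × 0.10 × 0.90/75) = 0.0490 and the unpooled one is √((0.0475 + 0.1275)/75) = 0.0483. Power = Φ((0.10 − 1.96 × 0.0490)/0.0483) ≈ 0.53.

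**5. Whether the cost questionnaire could serve instead.** TiC-P asks about the past four weeks, so T1 to T3 cover 3 × 4 = 12 of the 30 weeks. The article does not list crisis or hospital contacts among its items.

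**The case against.** The strongest reply is that much of this is silence in a condensed article. An adverse-effect definition, instrument or reporting procedure may be in the full protocol, which is not shown. That stands: the absence of such a procedure is not the point made here.

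Three stronger readings are tempting, and the article does not support them.

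- A reader might infer that adverse effects will be read off the platform logs, which exist in one arm only. No sentence says so. The source sentence covers process data as a whole, and usage statistics fit session counts and time investment better.
- A reader might treat the ten interviews per arm as the harm sample and calculate how many events they would miss. The article gives their subject as feasibility and usability and does not present them as a way of finding adverse effects.
- A reader might conclude that harm cannot be compared between arms at all. That goes too far. Withdrawal reasons are collected in both arms. The IDS-SR, EQ-5D and SF-36 follow one schedule in both arms, and the QIDS-SR is used in both with weekly completion encouraged. The full MINI at T3 is done by blinded assessors.

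It is also fair that the trial is a pilot without hypothesis tests, that its primary analyses are economic, and that the IDS-SR is self-reported by unblinded patients. These limit what a deterioration comparison can show. They do not remove the gap: the plan collects suitable data and states no patient-level comparison of worsening from them.

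**Conclusion.** The point holds in a limited form. The article fixes no like-for-like comparison of harm. Adverse effects sit under sources not described as eliciting harm from all patients, capture from those sources may differ by arm in an unknown direction, and no planned outcome counts patients who worsen.

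The size of any distortion cannot be derived from the article. The ratio of 1.6 (or 0.625) rests entirely on the assumed capture of 80% against 50%. The 10-week difference in contact rests on the ten weeks given for bCBT in the Interventions section and in the Discussion; the Abstract's description of alternating weekly sessions could be read as a longer course.

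A deterioration comparison would itself be imprecise: about ±7 to ±10 percentage points at assumed rates of 5% to 10%, and about 53% power for 5% against 15%, before attrition. The primary economic analysis is unaffected. The change is worth making because it alters what the trial can say about harm.

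**What to change.** In Process data and in Explorative analyses, add patient-level deterioration: an IDS-SR increase from baseline above a reliable-change threshold at T1, T2 and T3. Fix the threshold in advance, for example 1.96 × SD × √(2 × (1 − reliability)), with the baseline SD and a stated reliability; the article gives neither value, so the number of points cannot be set here.

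Report counts and 95% confidence intervals by arm, with T3 as the main comparison. At week 30 planned treatment has ended in both arms, whereas week 10 sets the end of treatment in bCBT against mid-treatment in CBTAU. Even at T3 the time since planned treatment end differs (20 weeks against 10), and the report should say so. State how patients with a missing IDS-SR are counted, consistent with the imputation already planned.

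Keep process-source adverse effects and withdrawal reasons as supplementary description. If TiC-P contacts are shown beside them, state that they cover only the four weeks before each assessment.

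The cost is some wording and one short table from data already collected. Recruitment was ongoing when the article was written, so the definition could still be fixed before results are known. The downsides are imprecision at 75 per arm, self-report by unblinded patients, and a result that may look less favourable than response and remission alone.

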### Sample size

Given the nature of our pilot study, we chose to conduct a cost-effectiveness study, in which we focus on the probability of cost-effectiveness of bCBT in comparison with CBTAU for various ‘willingness to pay’ ceilings, i.e., the cost-effectiveness acceptability curve (CEAC; Fenwick et al. 2001). The probabilistic assessment does not entail hypothesis testing. Instead, the outcomes will be presented as the likelihood (in %) that bCBT is superior to CBTAU in terms of cost-effectiveness [18].

Through a simulation study, we determined the impact of various sample sizes on the stability of the CEAC. Using realistic fixed estimates of the mean and standard deviation of effects and costs at population level (based on Hakkaart-van Roijen et al., 2006), we simulated a large number of trials in which we systematically varied sample sizes between n = 10 to n = 500 per group (n = 10, 25, 50, 75, 150, 500). As expected, the stability of the CEAC improved with increasing sample size. Below n ≤50, probability estimates were highly unstable. At a sample size of n = 75 per group, however, we found probability estimates to converge to acceptable 75% percentile ranges within the relevant range of willingness to pay ceilings. Therefore, for this study, we settled for a sample size of N = 150 (n = 75 per group).

### Statistical analyses

#### Primary analyses

A cost-effectiveness analysis (CEA) and cost-utility analysis (CUA) will be conducted from both the health care perspective and the societal perspective. Therefore, we will take direct medical costs, direct non-medical costs and indirect medical costs into account. In addition, a budget impact analysis (BIA) will be based on a health-economic modelling study based on Mauskopf’s recommendations [32]. Based on the BIA, expected costs to the public purse, the health care insurer and the service-provider will be estimated.

#### Cost-effectiveness and cost-utility analyses

The *cost-effectiveness analysis* (CEA) will be based on treatment response. Analyses will be conducted for both treatment response, defined as a 50% pre-post reduction of IDS-SR depressive symptoms [40,42], assessed as the DSM-IV depression status at 30 weeks, as measured by the MINI plus interview [35].

The *cost-utility analysis* (CUA) will be conducted using quality adjusted life years (QALYs) as a generic measurement of health gains, based on EQ-5D [45,46] and SF-36 data [49,50,53].

In order to obtain the costs per treatment responder and the costs per QALY gained, the incremental cost-effectiveness ratio (ICER) will be computed using the bootstrap method. The simulated ICERs will then be projected onto the cost-effectiveness plane and presented as acceptability curves.

For decision-making purposes, the ICER acceptability curve will be plotted using various willingness-to-pay (WTP) ceilings, which supports analysis as to whether the blended intervention offers good value for money, compared with CBT treatment as usual. One-way sensitivity analyses directed at uncertainty in the main cost drivers will be performed to assess the robustness of our findings across a range of likely values for those parameters.

#### Budget impact analysis

To assess the impact of blended CBT for depression compared with CBT as usual on health care budgets, a *budget impact analysis* (BIA) will be conducted as outlined by Mauskopf et al. [32]. The BIA will assess the impact on 1) wider society (including productivity losses), 2) the public purse, and 3) health insurers and health care service providers. When taking the public purse and health insurance companies into account, the focus will be restricted to direct medical costs. For each angle, we assess costs when 10%, 20%, 30% and 100% of the target group receive bCBT. These scenarios will be compared with the baseline scenario, reflecting current care, where 0% of the target group is offered bCBT.

Regarding the costs to wider society, we will assess the costs of offering the health care interventions, as well as the interventions offered in routine specialized mental health care for this particular target group, patients’ out of pocket expenses, and costs arising from productivity losses.

The BIA will be conducted using a health economic (Markov cohort) simulation model, called DepMod [16]. The model is based on the epidemiology of depressive disorder as obtained from the population-based NEMESIS psychiatric cohort study [65]. DepMod compares two health care systems: care-as-usual for depressive disorder and the alternative health care scenario with blended cognitive behavioural treatment. Costs and effects will be modelled for the short term (1 year) and longer term (5 years), at national level, as well as those incurred by the health care provider and health insurance company. Long-term costs and effects will be discounted in accordance with the Dutch guidelines [55]. DepMod involves extensive sensitivity analyses that cover cost, effect and discounting parameters simultaneously [66].

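### The 5-year budget impact figures for the public purse, insurer and provider are discounted, so they understate the outlay or saving in each year after the first

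*Protocol article*

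**What the plan says.** All references are to the Protocol article.

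- **Purpose.** The Budget impact analysis section opens "To assess the impact of blended CBT for depression compared with CBT as usual on health care budgets". It names three angles: wider society, the public purse, and insurers together with service providers. The Primary analyses section says that, from this analysis, "expected costs to the public purse, the health care insurer and the service-provider will be estimated".
- **Scenarios.** Uptake of 10%, 20%, 30% and 100% is compared with 0%, for each angle.
- **Model and horizon.** "The BIA will be conducted using a health economic (Markov cohort) simulation model, called DepMod [16". On the horizon: "Costs and effects will be modelled for the short term (1 year) and longer term (5 years), at national level". The same sentence goes on to include the costs met by the provider and the insurance company.
- **Discounting.** The next sentence is "Long-term costs and effects will be discounted in accordance with the Dutch guidelines [55". It separates neither the societal angle from the payer angles nor costs per effect from budget outlays. The rate is left to the cited guideline.
- **Sensitivity.** "DepMod involves extensive sensitivity analyses that cover cost, effect and discounting parameters simultaneously [66". A zero rate is not mentioned.

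**The concern.** A budget impact analysis and a modelled cost-effectiveness analysis answer different questions. The first tells a payer how much money will leave or stay in its budget in a given year. The second weighs costs and effects that fall at different times, and there a present value is the natural scale. An insurer planning for year 5 must fund the amount due in year 5, not its value today.

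The protocol states the first question as the purpose for the payer angles, then applies the scale of the second to the 5-year costs. What is at stake is the use of the 5-year payer figures. The Strengths and weaknesses section says the budget impact analyses are meant to inform stakeholders, insurers and providers among them. Read as planned spending, discounted figures would be too small in absolute size in every year after the first, whether the net impact is a cost or a saving.

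**Working it through.** The protocol gives no numerical budget impact result, so there is no figure to reproduce. The check is how far discounting moves a payer's amount away from cash.

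**Inputs**
- Horizon: 5 years (Budget impact analysis section).
- Discount rate r: not stated. Assumed at 1.5%, 3%, 4% and 5% per year to show a range.
- Timing: not stated. Main calculation with year 1 undiscounted; end-of-year timing as a check.
- Cash flow: 100 units per year, constant, for illustration. Undiscounted, this is 100 in each year and 500 in total.

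**Formulas (year 1 undiscounted)**
- Factor for year k: 1/(1+r)^(k−1).
- Year-5 shortfall: 1 − 1/(1+r)^4.
- Shortfall of the 5-year total: 1 − (sum of the five factors)/5.

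**Results**

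| r | Factors, years 1 to 5 | 5-year total (500 in cash) | Total understated by | Year 5 understated by |
|---|---|---|---|---|
| 1.5% | 1, 0.9852, 0.9707, 0.9563, 0.9422 | 485.4 | 2.9% | 5.8% |
| 3% | 1, 0.9709, 0.9426, 0.9151, 0.8885 | 471.7 | 5.7% | 11.2% |
| 4% | 1, 0.9615, 0.9246, 0.8890, 0.8548 | 463.0 | 7.4% | 14.5% |
| 5% | 1, 0.9524, 0.9070, 0.8638, 0.8227 | 454.6 | 9.1% | 17.7% |

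**Timing check.** If flows are placed at the end of each year, the 5-year totals become 478.3 at 1.5% (4.3% low) and 432.9 at 5% (13.4% low). Year 5 is then low by 1 − 1/1.015^5 = 7.2% and by 1 − 1/1.05^5 = 1 − 0.7835 = 21.6%. The main calculation is therefore the milder of the two.

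**Scenario differences.** Each year's difference between an uptake scenario and 0% uptake is multiplied by that year's factor, so the differences shrink in the same way. With a constant net yearly flow, neither the sign nor the ranking of the scenarios changes.

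**Direction.** Suppose an up-front cost C is followed by a constant yearly saving S in years 1 to 5. In cash, break-even is C = 5.00 S. Discounted, it is C = S × (sum of factors): 4.85 S at 1.5%, 4.63 S at 4% and 4.55 S at 5%. Only a C between that value and 5.00 S turns a cash saving into a discounted loss. If savings came first and costs later, the shift would go the other way.

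**The case against.** The strongest reply has four parts.

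1. **The sentence may be a general DepMod setting.** It covers effects as well as costs, and the model produces both. Discounting suits modelled cost-per-effect results and is defensible for societal costs over 5 years. This stands, and it limits the point to the payer angles. It would be too much to infer that all discounting in this section is wrong, or that the rule acts only on budget figures.

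2. **The method and the rate are delegated to cited sources, and an article condenses its full plan.** Those sources are not at hand and might call for undiscounted yearly tables. But the article does not merely omit a table format. It states a discounting rule directly after the insurer and provider horizon, with no exception. A reader who follows the text would discount the payer costs.

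3. **Sensitivity analyses cover discounting.** They vary it together with costs and effects. The text promises no zero rate, and joint variation does not isolate the undiscounted outlay.

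4. **The trial's primary goal is untouched.** This is correct. The 30-week analyses need no discounting and the 1-year horizon is not affected, so the matter concerns reporting of the 5-year model.

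A reader might also infer that discounting tilts the result against blended CBT, since "the costs of developing and maintaining the online bCBT platform will be taken into account" and platform costs could fall early while savings come later. The documents do not support this. That sentence concerns intervention costs in the trial and names maintenance as well as development, so part of the cost recurs. Nothing says when platform costs enter DepMod or which payer bears them.

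**Conclusion.** The point holds for the public purse, insurer and provider over the 5-year horizon. The plan states a discounting rule that does not serve its own stated purpose for these angles, because a discounted amount is not the cost a budget holder will meet.

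At assumed rates of 1.5% to 5% with year 1 undiscounted, the year-5 outlay or saving is understated by 5.8% to 17.7% and a constant 5-year total by 2.9% to 9.1%. End-of-year timing would make this larger. The sizes rest on the assumed rate, the timing and a constant yearly flow. That each later year's amount shrinks towards zero rests only on a positive rate. If the yearly net impact changes sign over time, the 5-year net total need not move in one direction, so no bias for or against blended CBT can be claimed.

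**What to change.** In the Budget impact analysis section, replace the discounting sentence with wording such as:

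*For the public purse, the health insurer and the service provider, the main result is undiscounted costs per year (years 1 to 5) and their sum, for each uptake scenario. Discounting is applied to modelled cost-per-effect results from DepMod and to the societal perspective.*

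This keeps discounting where it fits and removes it only where the figure is meant to be a budget amount. It needs no new data and changes nothing in trial conduct. The cost is one further DepMod output with the cost discount rate set to 0. The report will then carry two sets of 5-year figures, which must be labelled clearly so that a cash total is not compared with a present value.
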